## Abstract

**Background:**

Overall, 55% of the German population suffers from primary episodic headaches according to recent studies. Inadequate management of headache disorders is a significant medical problem. The prevalence of medication overuse headache (MOH) is about 1% with an estimated number of 800,000 people in Germany. Medication overuse (MO) and MOH are usually managed through a complex process of medication withdrawal and initiating of prophylaxis. However, patients who were successfully treated for MO or MOH have a high relapse rate in the following 2 years. Previously, continued monitoring of self-reported medication intake demonstrated lower relapse rates. The prevalence and burden of MO and MOH are high, and effective strategies to prevent the development of a relapse into MOH or de novo MOH are still missing. Therefore, the MOH trial was designed to assess the effects of combining self-reported medication intake with daily monitoring of the entered data and a personalized patient-specific medication intake feedback system in an easy-accessible app-based platform in order to prevent the development and relapse of MO(H).

**Methods:**

The MOH trial is a randomized, controlled, parallel, multicenter, prospective trial. A total of 624 migraine patients with frequent migraine attacks and 336 patients who underwent treatment for MO(H) will be randomly allocated to use either a customized app with or without individual feedback regarding their self-reported medication intake for 12 months. The primary outcome will be the proportion of patients developing MO or MOH for at least 3 consecutive months between baseline and end of study visits.

**Discussion:**

This trial will assess the effects of providing patients with feedback regarding their self-reported use of migraine medications and migraine days using a mobile software on the development or prevention of MO(H). We hypothesize that the development of MO(H) in patients with frequent episodic migraine (EM) or chronic migraine (CM) and relapse after treatment of MO(H) can be reduced by a feedback system. If this trial proves that using an app with specific and unspecific messaging to the patient is successful, this method, which is now investigated mainly in specialized headache centers, could later be extended to primary care, thus providing benefits for a broader patient group.

**Trial registration:**

German Clinical Trials Register DRKS00025961. Registered on 04 August 2021.

## Administrative information

Note: the numbers in curly brackets in this protocol refer to SPIRIT checklist item numbers. The order of the items has been modified to group similar items (see http://www.equator-network.org/reporting-guidelines/spirit-2013-statement-defining-standard-protocol-items-for-clinical-trials/).

## Introduction

### Background and rationale {6a}

Overall, 55% of the German population suffers from primary episodic headaches mostly migraine and tension-type headache according to recent studies [1]. Inadequate pain management is a significant medical problem. The prevalence of medication overuse headache (MOH) is about 1%. In Germany, an estimated number of 800,000 people are affected [1]. Treatment guidelines including self-medication are available [2] and many patients with chronic headaches take abortive medications daily or almost daily. Medication overuse (MO) through frequent or regular intake of medications to treat acute headache episodes may lead to an increase in headache frequency and eventually to a transition from episodic to chronic headache. Furthermore, patients with frequent migraine attacks are at risk to overuse medication for the treatment of migraine attacks and to develop MOH, a condition in which the treatment becomes the cause of the disease. MO and MOH are usually managed through a complex process of medication pause or withdrawal. However, patients who were successfully treated for MO have a relapse rate of up to 50% in the following 2 years [3–6]. The optimal approach to this important clinical problem is to prevent patients from developing initial episodic migraine (EM) through MO into chronic migraine (CM) and MOH. Currently, individuals who overuse prescription medications can be identified through integrated headache centers and pharmacy data. However, this is difficult for individuals who overuse over the counter (OTC) medications unless medication self-report is accurate and sustained over time. Mobile electronic software devices are now ubiquitous and are powerful tools for collecting such data. Older systems such as electronic diaries, incorporating feedback and alert systems, improved relapse rates in this population already with an odds ratio of 1.45, demonstrating the potential possibilities of a mobile, permanently accessible device [7].

Until now, only one prospective study has investigated the value of electronically assisted monitoring, advice, and communication in improving the outcome (number of subjects who remained overuse-free without relapses over a follow-up of 6 months) in a controlled, multicenter, multinational trial conducted in six headache centers located in Europe and Latin America [7]. In this trial, 663 MOH subjects were enrolled and divided into two groups: the intervention group, i.e., “COMOESTAS group,” was monitored with an electronic diary associated with an alert system and a facilitated communication option, and the Classic group equipped with a paper headache diary. As a result, a significantly higher percentage of overuse-free subjects was observed in the COMOESTAS group compared to the Classic group (odds ratio 1.45, *p* = 0.046). The COMOESTAS group performed better, also in terms of the number of days/month with acute medication use and the degree of disability. This trial included only patients with manifest MOH and did not investigate whether modern app-based headache monitoring systems can prevent the development of MOH in patients with frequent episodic or chronic migraine. In addition, no study to date has examined the efficacy of an app-based feedback system for relapse prevention after successful withdrawal therapy in patients with MOH. Collectively, although the prevalence and burden of MO and MOH are high, effective strategies to prevent the development of a relapse into MOH are still missing.

This trial will assess the effects of providing patients with feedback regarding their self-reported use of migraine medications and migraine days using a mobile software application (app; called N1-Headache) on the development or prevention of MOH. We hypothesize that the development of MO or MOH in patients with frequent EM or CM and relapse after treatment of MO(H) can be reduced by a feedback system.

If this trial proves that using an app with specific and unspecific messaging to the patient is successful, this method, which is now investigated mainly in specialized headache centers, could later be extended to primary care, thus providing benefits for a broad patient group.

### Objectives {7}

The trial objective is to assess whether transition from frequent EM or CM to MO or MOH or relapse after treatment of MO(H) can be reduced by a feedback system of a mobile application.

### Trial design {8}

This trial will be conducted according to the professional code for physicians in Germany §15 and is designed as a randomized, controlled, parallel, allocation-blinded multicenter, prospective trial with two arms. The effects of providing feedback to migraine patients regarding their self-reported use of migraine medications will be monitored using the app “N1-Headache” on the development of MO or MOH over 12 months after randomization.

Patients with qualifying migraine or a history of MO(H) will be recruited in different ways: First, through their physician at a participating headache center or medical practice. Second, through an advertisement for this trial sent by Curelator to German-speaking users of the public available Curelator app, directing interested patients to a participating site. Third, through cooperation with the German Headache Society (DMKG) and the MigräneLiga e.V, a self-help organization who will provide information about the trial within the respective section on their homepage. In addition, some study sites might publish a pre-approved template on their homepage to inform about the trial.

Informed consent will be obtained in the participating center through the investigator and a screening for the inclusion and exclusion criteria will be carried out. Medical history will be assessed for the determination of headache type and current treatment as well as actual medication intake. To facilitate the documentation of medication, the attack aborting medication documented during the screening visit will be handed out to patients as a printout to be entered in the app.

After patients have completed a screening phase of 28 days with a sufficient level of compliance (≥80% days of recording headache and medication use) and if the inclusion and exclusion criteria are still fulfilled, they will be allocated to one condition (migraine patients or post-MO(H) patients) and subsequently randomized into one of the two study groups (control group or intervention group). The control group will receive unspecific messages providing information on general trigger factors or latest migraine research highlights. The intervention group will receive the same unspecific messages and also direct feedback on their medication use through warning messages when predefined limits of frequent medication use are reached or passed.

If MO or MOH, based on the defined primary outcome parameters, will occur during the trial, patients and investigators will be informed about the outcome. After that, the patients will receive the usual treatment program for MO or MOH, but remain in the study for secondary endpoint documentation.

Similar to a comprehensive cohort study design, patients, who are eligible for the study but do not like to participate, should be asked to give consent to a baseline data capture and a follow-up questionnaire after 6 and 12 months. This group will be able to represent an external control group, that is not using the app and is receiving no messages at all.

A flowchart of the study is presented in Fig. 1

**Fig. 1 Fig1:**
[figure not shown]
Flow chart of the MOH-DE trial process from screening to data analysis

## Methods: Participants, interventions, and outcomes

### Study setting {9}

Patients will be recruited from about 30 sites in Germany. The sites are composed of university hospitals, headache centers, and private practices with long-standing experience in the management of migraine patients. Most of these centers were part of the German Headache Consortium funded by the German Ministry of Education and Research (BMBF), participated in recent DFG-BMBF-funded headache trials or were part of study groups led by the PI of this study with CGRP-monoclonal antibodies or treatment devices (transcutaneous vagus stimulation). The list of participating sites will be presented in the German Clinical Trial register.

### Eligibility criteria {10}

#### Inclusion criteria

Migraine patients: patients with frequent EM (≥ 8–14 headache days/month, of which 4 fulfill IHS criteria for migraine) or CM (≥15 headache days/month, of which 8 fulfill criteria for migraine) OR Post-MO(H)-patients: patient who underwent treatment for MO(H) (initially ≥ 15 headache days/month, intake of attack aborting medication on 10 or more or 15 or more days/month according to ICHD-3 criteria of MOH) AND 2)Owning a mobile device with an iOS or Android system, which is able to run the app3)Adults ≥ 18 years4)Written informed consent consistent with ICH-GCP guidelines and local laws signed prior to all study-related procedures5)Compliance for using the app on ≥ 80% days during the screening period

#### Exclusion criteria

Patients with concomitant primary headache disorders, other than EM or CM (except episodic tension-type headache < 15 days/month)Current MO upon the discretion of the treating physician (intake of attack aborting medication on ≥10 days/month within the last 3 months)Co-morbidity interfering with the study outcomes upon the discretion of the treating physicianIntake of opioids on > 3 days/monthRegular intake (> 15 days/month) of either (i) hypnotics or (ii) benzodiazepines as sedatives (tranquillizer) or (iii) antipsychotics (neuroleptics) due to a psychiatric indicationParallel use of other migraine apps to track headache days and medication intake

### Who will take informed consent? {26a}

Eligible patients will be approached by the study team and informed about the trial with a comprehensive patient information. After a point-by-point check of inclusion and exclusion criteria, informed consent will be obtained in the participating center through the investigator prior to enrollment and all trial-related procedures. The process of obtaining informed consent follows GCP guidelines, recommendations, and requirements. Only patients capable of giving consent by themselves are included in the trial.

### Additional consent provisions for collection and use of participant data and biological specimens {26b}

Not applicable as no biological specimens are collected as part of this trial.

## Interventions

### Explanation for the choice of comparators {6b}

Keeping a diary is a well-established instrument for migraine patients to document headache days and medication intake. While paper-based diaries have been state-of-the-art for many years, mobile applications are the predominant solutions nowadays to collect patient-reported data. Thus, using the same app-based electronic diary, which is capable of tracking headache days as well as medication intake, is an adequate comparator. The app of the control group will have the same features as the intervention group except the alert tool. For compliance reasons (to induce a level of interaction), the control group will receive monthly unspecific messages about current migraine news of interest. Besides the possibility to track many optional factors, patients might recognize the app as more than just a passive diary tool if they actively receive messages from time to time.

### Intervention description {11a}

N1-Headache is a digital platform (consisting of the N1-Headache app and the N1-Headache dashboard) that allows individuals with a history of migraine to track their headache outcomes (e.g., frequency, severity, and duration of attacks), migraine-related disability, medication use, and their potential migraine risk factors. For the MOH-DE study, the commercially available N1 platform was modified (e.g., onboarding and daily questionnaire, app settings, feedback customization) to comply with necessary study-specific adjustments and requirements.

Daily tracking of headache days, medication, and headaches and migraine risk factors is done through a visual interface that uses Visual Migraine Language^TM^ (VML), a set of icons developed with headache specialists and designed to facilitate the data entry of migraine symptoms and up to 70 migraine attack-related risk factors selected from a presented list, plus any custom factors the individual wants to track. Significant associations are presented to the user as a set of maps designed to show the results of their personal risk factor analysis.

The app is self-explanatory with a help icon behind each question where a detailed description of the question or answers is provided. In addition, a manual with all important questions is linked within the app.

Unspecific messages providing information on general trigger factors for migraine attacks or the latest migraine research highlights will be sent once a month to both groups to increase the general engagement with the app.

The intervention will be applied by means of alerts about the risk of overuse of certain classes of medication commonly used to treat headache/migraine or other conditions but which may also cause medication overuse headache. N1-Headache calculates the current risk of MO based on all the medications taken by an individual to treat migraine attacks and sends alerts to the user. Thresholds have been defined in accordance with the current ICHD-3 guidelines and are the same for all patients in the intervention arm.

### Criteria for discontinuing or modifying allocated interventions {11b}

There is no planned scenario in which the allocated intervention is modified or discontinued unless patients withdraw consent or the intervention cannot be continued due to protocol violations or dropouts.

### Strategies to improve adherence to interventions {11c}

Different measures are implemented to improve intervention adherence. (I) App compliance will be automatically analyzed and patients will be contacted by participating sites in accordance with a standardized procedure if the compliance drops below 80%. (II) Regular study visits are implemented in the study protocol to provide patients the opportunity to speak to investigators and vice versa. (III) In case that patients in the intervention group receive alert messages regarding their medication intake, they will get short-term appointments to see the investigator at the specific study site. (IV) The unspecific messages are designed to have an informative and a motivational character at the same time. (V) Daily reminders will be presented to the patients via the app if no data was entered on that day. If no data was entered on consecutive days, reminder messages will have an escalating character. (VI) Patients have the possibility to enable optional tools in the app, which are not part of the data export, but might be interesting for individual participants. Those tools can provide information and connections between factors of daily life and migraine or headache, such as nutrition, physical activity, or menstrual cycle.

### Relevant concomitant care permitted or prohibited during the trial {11d}

Intake of opioids (on > 3 days/month) as well as the regular intake (> 15 days/month) of either (i) hypnotics or (ii) benzodiazepines as sedatives (tranquillizer) or (iii) antipsychotics (neuroleptics) due to psychiatric disease is not allowed for study inclusion. If thresholds are exceeded or prescription reasons change during the trial, the patient will remain in the study unless the treating physician recommends study withdrawal. The patients will be analyzed in the ITT analysis set. Other than that, all concomitant medications are permitted and can be prescribed by the treating physician based on the underlying medical condition and upon the discretion of the treating physician. Any relevant medications that the participant is receiving at the time of enrollment or receives during the study will be documented.

### Provisions for post-trial care {30}

After individual trial completion, patients will have the option to use the publicly available version of the app for 1 year. After the trial, patients will receive standardized treatment for the appropriate indication through their general practitioner or treating neurologist.

### Outcomes {12}

#### Primary outcome

The primary outcome was defined due to its relevance to estimating MO prevalence and the associated costs [8].Proportion of patients developing MO or MOH for at least 3 consecutive months between baseline and end of study visits.

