#### Secondary outcome

The secondary outcomes are derived from the CHMP Guidelines on clinical investigations of migraine [9] and include:Number of headache days/monthNumber of days with attack aborting medication per monthTime to MO or MOHSeverity of headachesDisability due to headache (Migraine-specific disability assessment (MIDAS)-Score)Psychiatric comorbidity (Depression, Anxiety, and Stress Scale (DASS)-Score)Frequency of serious adverse events (SAEs)For patients who have reached the primary endpoint during the study: number of headache days/month and number of days with attack aborting therapy per month in the last study month

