#### Outcome assessment

Relevant clinical data and additional lifestyle factors include information about depression, anxiety disorder, chronic back pain, sport activities, smoking, and drinking behavior as well as shift work.

The primary outcome is MO or MOH defined according to International Classification of Headache Disorders (ICHD-3, 8.2) criteria of MO and MOH [13]. According to ICHD-3, MO is defined as regular overuse of acute or symptomatic headache medication (on ≥ 10 days/month with specific migraine medication or ≥15 days/month of simple analgesics) for more than 3 months and MOH is defined as headache occurring on 15 or more days/month in a patient with a pre-existing primary headache and developing as a consequence of MO. In this study, the primary endpoint is reached when the intake thresholds or headache days are exceeded for ≥ 3 months [8].

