#### Secondary outcome

All secondary analyses will be explorative, i.e., without adjustment for multiplicity using standard methods of inferential statistics appropriate for the given scale level of the outcome. Time to MO or MOH will be compared between groups using the log-rank test. Cox proportional-hazard model will be conducted to analyze the association between time to MO or MOH and (independent) predictor variables. Possible spontaneous improvement rates as well as response rates in the control group will be analyzed in order to assess the extent of unspecific migraine monitoring.

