## Discussion

The presented study will be the first randomized trial to use an app-based feedback system for the prevention of MO and MOH and the relapse after successful treatment of MOH. In addition to the control group, this study will also build an external control group, which will add great value in sensitivity analysis after completion of the trial. These are patients who are eligible based on the inclusion/exclusion criteria but do not agree to participate because they are not willing to document headache days and medication intake on a daily basis. In case the trial is positive, this has major implications for the care of migraine patients.

As MOH and MO are frequent among patients with high frequency episodic or chronic migraine and the total number of patients is high, there is a need to develop easy instruments for monitoring of those patients and prevent them for a relapse after withdrawn of overused medication. As had been shown, a systematic, structured follow-up may reduce the number of relapse [17]. However, due to the high number of affected patients, a less intense and cost-effective follow-up is necessary. Therefore, a self-monitoring of the patients using an electronic device might be very helpful. The aim of the study is to demonstrate the efficacy of a mobile device (app) including a headache diary and warning message in case of high use of acute medication.

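### Outcome assessment defines the primary endpoint in two incompatible ways, and under either one no listed outcome isolates MOH, so the trial can be positive with no difference in MOH

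*Protocol article*

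**What the plan says.** All references are to the protocol article.

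- **Primary outcome (Outcomes {12}).** "Proportion of patients developing MO or MOH for at least 3 consecutive months between baseline and end of study visits". The section justifies this choice by its relevance to MO prevalence and cost.
- **Outcome assessment (under {18a}), definitions.** "MO is defined as regular overuse of acute or symptomatic headache medication", with monthly intake-day thresholds of 10 (specific migraine medication) or 15 (simple analgesics). MOH needs at least 15 headache days a month "in a patient with a pre-existing primary headache and developing as a consequence of MO".
- **Outcome assessment, working rule.** The sentence after the definitions reads "In this study, the primary endpoint is reached when the intake thresholds or headache days are exceeded for ≥ 3 months".
- **Secondary outcomes.** These are headache days, acute-medication days, "Time to MO or MOH", severity, MIDAS, DASS and SAEs. For patients who reached the primary endpoint there is also "number of headache days/month and number of days with attack aborting therapy per month in the last study month". All secondary analyses are explorative.
- **Sample size {14}.** The migraine category is sized on a 10% yearly transition to MOH and a 6-point difference in MOH occurrence. The post-MO(H) category is sized on relapse of MO(H).
- **Discussion.** The trial is presented as testing "an app-based feedback system for the prevention of MO and MOH".

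**The concern.** The endpoint carries two labels, and the article does not settle what the second one adds. By the definitions, MOH adds no patient to MO. By the working rule, headache days alone could make a patient an event. These are different endpoints with different event rates, and only one can be the endpoint that was sized.

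Whichever is meant, MOH is never counted by itself. The time-to-event outcome uses the same composite. The alerts respond to recorded medication use, and the endpoint is derived from what patients enter in the app. The arms could therefore differ in recorded intake days while equal numbers go on to MOH. The migraine sample-size text, read literally, would lead a reader to take the 80% power as power for MOH, and a positive result as evidence that MOH was prevented. The listed outcomes would not directly confirm or refute that.

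**Working it through.** **1. The plan's own figures.** Inputs from Sample size {14} and the statistical methods: two-sided α = 0.05, power 0.80, 1:1 allocation, 10% vs 4% (migraine) and 40% vs 25% (post-MO(H)). For the pooled z-test, with p̄ the mean of the two rates,

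n per arm = [1.96·√(2p̄(1−p̄)) + 0.8416·√(p₁(1−p₁)+p₂(1−p₂))]² / (p₁−p₂)²

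- Migraine: [1.96·√0.1302 + 0.8416·√0.1284]² / 0.06² = 1.0177/0.0036 = 282.7, so 283.
- Post-MO(H): [1.96·√0.43875 + 0.8416·√0.4275]² / 0.15² = 3.4171/0.0225 = 151.9, so 152.

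Both agree with the article.

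**2. The two endpoint rules side by side.**

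| Patient, over three months | MO or MOH by the definitions | Intake or headache days by the working rule |
|---|---|---|
| Overuse, under 15 headache days/month | event | event |
| Overuse, 15 or more headache days/month | event | event |
| No overuse, headache days above the threshold | no event | event |

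The first column equals MO. The second adds the last row. Chronic migraine patients are eligible with 15 or more headache days at entry, so they could fall in that row without overusing. Neither column separates row two, which is where MOH lies.

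**3. Positive result, no MOH difference.**

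- Migraine: MOH 2% vs 2%, MO without MOH 8% vs 2%. Composite: 10% vs 4%.
- Post-MO(H): MOH 10% vs 10%, MO without MOH 30% vs 15%. Composite: 40% vs 25%.

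The composite rates are the planned ones, so power stays at 80%. In counts at 312 per migraine arm (624/2), about 31 vs 12 events: pooled rate 43/624 = 0.0689, difference 19/312 = 0.0609, SE = √(0.0689·0.9311·2/312) = 0.0203, z = 3.00, Pearson p = 0.0027. About 6 MOH cases could sit in each arm.

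**4. Power for MOH alone.** The article does not give the MOH share of events. Assume 30%, 50% or 70%, with the same relative reduction as the composite. Power is by enumeration of the two binomials with the Pearson test.

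| MOH share (assumed) | Migraine rates | 283/arm | 312/arm | Post-MO(H) rates | 152/arm | 168/arm |
|---|---|---|---|---|---|---|
| 30% | 3.0% vs 1.2% | 32% | 35% | 12.0% vs 7.5% | 26% | 29% |
| 50% | 5.0% vs 2.0% | 50% | 54% | 20.0% vs 12.5% | 43% | 46% |
| 70% | 7.0% vs 2.8% | 65% | 70% | 28.0% vs 17.5% | 59% | 64% |

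The larger sizes assume no loss to follow-up. The stated 283 and 152 are the relevant ones.

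**5. What the literal working rule would do to the primary test.** Suppose a share c of migraine patients are chronic migraine entrants who meet the headache-day limb in either arm regardless of treatment. The rates become c + (1−c)·0.10 and c + (1−c)·0.04. The article does not give c.

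| c (assumed) | Rates | Power at 283/arm |
|---|---|---|
| 5% | 14.5% vs 8.8% | 56% |
| 10% | 19.0% vs 13.6% | 41% |
| 20% | 28.0% vs 23.2% | 26% |
| 30% | 37.0% vs 32.8% | 18% |

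The choice of rule therefore affects the primary analysis as well as the labels.

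**The case against.** **The stated question is MO or MOH.** The objective, the hypotheses and the primary outcome all name the composite, and the outcome is justified by MO prevalence and cost. A result driven by MO answers that question. This stands: the primary test is not invalid, and the point concerns definition and interpretation.

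**Headache outcomes are already planned.** A reader might infer that nothing in the plan could reveal fewer medication days without headache benefit. The article does not support that. Headache days, severity and MIDAS are listed for all patients and would partly show it, and a subgroup analysis by baseline headache days is planned. But these are indirect: they do not tie headache days to overuse in the same months. The last-month outcome is limited to patients who reached the endpoint, a group formed after randomisation.

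**The endpoint might simply be MO.** A reader might infer from the definitions that the MOH limb adds no event and that the outcome is intake alone. The working rule prevents that as a settled conclusion. Equally, the primary outcome speaks of patients developing MO or MOH, which sits badly with counting chronic migraine entrants already at 15 headache days. The text does not decide between the two.

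**Components may be left to the SAP.** Their presentation may be. But the contradiction and the MOH wording of the migraine sizing are in the article itself.

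**The equal-MOH scenario is constructed.** It is. It shows what the endpoint permits, not what is likely.

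**Conclusion.** The point holds as a contradiction in the endpoint rule combined with a missing MOH outcome. By the definitions the primary endpoint is MO; by the working rule it is MO or frequent headache. Under neither is MOH counted separately, and a positive trial is compatible with no MOH difference. The 80% power belongs to the composite at the planned rates. For MOH alone it would be about 32% to 65% (migraine) and 26% to 59% (post-MO(H)) at the stated sizes, if MOH is 30% to 70% of events with an equal relative effect; both conditions are assumptions. The loss of power under the literal working rule likewise depends on an assumed share of chronic migraine entrants. It would be too strong to say that the trial fails its formal objective or that its headache outcomes carry no information.

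**What to change.** 1. Reconcile the definitions and the working rule in Outcome assessment into one endpoint rule. Say whether headache days without overuse count, and how chronic migraine entrants are handled.
2. Pre-specify the proportion with MOH (overuse together with at least 15 headache days a month in the same three months) as a named exploratory secondary outcome in each category. Report the arm difference with a confidence interval, and report patients entering with episodic migraine separately, since chronic migraine patients already meet the headache-day count at entry.
3. Classify MOH at the endpoint event. Trial design {8} says patients who reach the endpoint are informed and then receive the usual treatment programme, so later MOH is affected by that treatment.
4. Align the migraine wording in Sample size {14} with the endpoint actually tested.
5. State that a primary result driven by intake supports a conclusion on medication overuse, and that any conclusion on MOH rests on the MOH result.

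**Cost.** Protocol and SAP text only; daily headache and medication entries are already captured in the app. The MOH estimate will be imprecise, as the power figures show, and the headline claim may narrow to medication overuse. If the single rule chosen is the wider one, the planned event rates and sample size need rechecking.
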